The majority of existing studies lack adequate sample sizes, only collect short-term outcomes, frequently examine dry needling as a stand-alone intervention, and only treat one muscle for one to two sessions, which is not consistent with how dry needling is commonly performed clinically. Typically, clinicians will perform an examination to locate active and latent MTrPs and needle numerous active trigger points in a single session. They may then dry needle the patient over many sessions to achieve optimal effects. With the high prevalence of neck pain and its contribution to prolonged disability in patients, it is essential to identify optimal treatment approaches [1-3,5,6,40,41]. Therefore, the aim of this randomized clinical trial is to examine the long-term effects of a combination of manual therapy, exercises, and dry needling to the cervicothoracic region on pain and disability in individuals with acute or chronic mechanical neck pain resulting from postural dysfunction, trauma, or insidious onset who are referred to physical therapy.

We hypothesize that patients who receive dry needling, manual therapy, and exercise will achieve greater reductions in pain and disability in the short term (ie, 4 weeks) and long term (ie, 6 and 12 months) compared to those who receive sham dry needling, manual therapy, and exercise.

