	After needle is removed, pressure with a cotton ball will be maintained to prevent excessive bleeding
	The number of sites and specific muscles treated will be recorded by the therapist
Trigger point assessment performed on the suboccipital muscles	Patient in prone, therapist identifies the hypersensitive spot in the suboccipital muscles
	The overlying skin will be cleansed with alcohol
	Once the needle has been inserted manually into the trigger point, the needle will be pistoned in an up-and-down fashion so that 2- to 3-mm vertical motions occur (ie, fast-in and fast-out technique as described by Hong) at approximately 1 Hz for 25-30 seconds, with the aim of eliciting local twitch responses
	After needle is removed, pressure with a cotton ball will be maintained to prevent excessive bleeding
	The number of sites and specific muscles treated will be recorded by the therapist

We will compare baseline variables between groups by using independent *t* tests or Mann-Whitney U tests for continuous data and chi-square tests of independence for categorical data. An intention-to-treat analysis will be utilized, in which all participants will be analyzed in the group to which they were originally assigned. All dropouts and the reasons for dropping out of the study will be reported. An a priori alpha level of .05 will be used for all analyses. All data will be checked to ensure they meet the assumptions for the inferential statistical analyses described below. If they do not meet the necessary assumptions, appropriate nonparametric procedures will be utilized. We will examine the primary aim with a two-way repeated-measures analysis of variance with treatment group (ie, manual therapy, exercise, and dry needling vs manual therapy, exercise, and sham dry needling) as the between-subjects independent variables and time (ie, baseline, 4 weeks, 6 months, and 12 months) as the within-subjects independent variable. The hypothesis of interest is the two-way group × time interaction. Bonferroni-corrected post hoc tests will be used to determine difference between group means.

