### Power Analysis

Sample size and power calculations were performed using G*Power version 2 statistical software (Heinrich-Heine- Universität Düsseldorf) based on the minimal clinical improvement of 12 points on the NDI [51,69], assuming a standard deviation of 16 points, two-tailed, and an alpha level of .05. This requires a minimum sample size of 29 subjects per group. A total of 76 patients with a primary complaint of neck pain who meet the inclusion/exclusion criteria and consent to participate will be enrolled into the study. This sample size will yield greater than 80% power to detect both statistically significant and clinically meaningful changes in the NDI; additionally, this will control for dropouts prior to the 4-week follow-up.

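### Holm's step-down procedure would be a cheap improvement on the named Bonferroni correction for the post hoc arm comparisons, with more power when benefit is present at several visits and the same familywise error

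*Protocol article*

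**What the plan says.** The Data Analysis section of the protocol article tests the primary aim with a two-way repeated-measures analysis of variance. The between-subjects factor is treatment group, and the second factor is "time (ie, baseline, 4 weeks, 6 months, and 12 months) as the within-subjects independent variable". It then says "The hypothesis of interest is the two-way group × time interaction", followed by "Bonferroni-corrected post hoc tests will be used to determine difference between group means". The general level is given as "An a priori alpha level of .05 will be used for all analyses".

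The hypothesis at the end of the Introduction, repeated in the Discussion, is specific to visits. It expects "greater reductions in pain and disability in the short term (ie, 4 weeks) and long term (ie, 6 and 12 months") with real rather than sham needling.

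The Power Analysis section sizes the trial "based on the minimal clinical improvement of 12 points on the NDI", "assuming a standard deviation of 16 points, two-tailed, and an alpha level of .05". It concludes: "This requires a minimum sample size of 29 subjects per group". Enrolment is set at 76, that is 38 per arm under the equal allocation given in the Intervention overview.

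**The concern.** The interaction is an omnibus test over four time points. It does not say at which visit the arms differ, or in which direction. The post hoc tests have to answer that, so they carry the separate statements about 4 weeks, 6 months and 12 months.

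With two arms, the most natural reading of the post hoc sentence is an arm comparison at each visit. Bonferroni then holds every comparison at the same reduced level, whatever the other visits show. Holm relaxes the level once a visit has been declared significant. Both procedures hold under any dependence between visits. What is at stake is efficiency: power that could be recovered at the later visits with no more patients and no loosening of error control.

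**Working it through.** **Inputs.** From the Power Analysis section: difference 12 NDI points, SD 16, two-sided alpha .05, 29 per arm required, 76 enrolled (38 per arm). Assumed, because the article does not state them: a family of three post-baseline comparisons, and a between-visit correlation of 0.5 (0 and 0.7 also tried).

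**Step 1: the plan's own figure.** The normal approximation gives n per arm = 2(1.960 + 0.842)² × 16²/12² = 2 × 7.85 × 1.778 = 27.9, so 28. The exact noncentral t calculation gives 29, as stated. At 38 per arm, power for one comparison at .05 is 89.7% (t), which agrees with the claim of more than 80%.

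**Step 2: per-visit power under Bonferroni (noncentral t).** The per-comparison level is .05/3 = .0167, or .05/4 = .0125 if baseline were counted as a fourth comparison.

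| Per arm | alpha .05 | alpha .0167 | alpha .0125 |
|---|---|---|---|
| 38 | 89.7% | 79.2% | 75.9% |
| 29 | 80.1% | 65.1% | 61.0% |

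The 29-per-arm row corresponds to a loss of (38 − 29)/38 = 23.7%.

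**Step 3: the two rules.** Bonferroni rejects each visit with p ≤ .0167. Holm orders the three p values and compares the smallest with .05/3 = .0167, the next with .05/2 = .025 and the largest with .05, stopping at the first failure. The first steps are identical, so the two rules can differ only after one visit has been declared significant.

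**Step 4: simulation.** 20,000 trials per setting, two-sample t test at each visit, SD 16, correlation 0.5. Dropout and any requirement that the interaction be significant first were not modelled. Such a requirement would apply equally to both rules, and Holm would still reject at least as much.

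| Per arm | True differences (4 wk/6 mo/12 mo) | Visit | Bonferroni | Holm |
|---|---|---|---|---|
| 38 | 12/12/12 | each | 79% | 86% |
| 29 | 12/12/12 | each | 65% | 73% |
| 38 | 12/10/8 | 12 months | about 40% | 53% |
| 38 | 12/6/6 | 4 weeks | 79% | 80% |
| 38 | 12/6/6 | 6 or 12 months | 22% | 29–30% |
| 38 | 12/0/0 | 4 weeks | 79.5% | 79.6% |

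With 12/12/12 and correlations from 0 to 0.7, Holm's per-visit power ranges over about 85–88% at 38 per arm and 72–75% at 29 per arm. Bonferroni stays near 79% and 65%.

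**Step 5: what does not change.** The chance of at least one significant visit is the same under both rules in every setting (for example 94.5% with 12/12/12 at 38 per arm). Familywise error when no visit has an effect is also the same, 4.0% to 5.0% across settings. With 12/0/0 at 38 per arm, the two null visits are rejected 1.5–1.6% of the time each under Bonferroni and 2.3% each under Holm. Their sum, 2 × 2.3% = 4.6%, stays within 5%.

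**The case against.** The strongest reply is that nothing here is wrong. Bonferroni is prespecified, standard and controls the familywise error strongly. The article does not promise the most powerful method, and the stated hypothesis of interest is the interaction at .05, which no post hoc correction touches. At the enrolled 38 per arm, Bonferroni over three visits still leaves about 79% power per visit for 12 points. It also supplies matching adjusted confidence intervals directly. All of this stands, and it is why the point is a suggested improvement.

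A reader might infer more in four ways that the document does not support:

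- **That power is lost at every visit.** Holm's first threshold is Bonferroni's, so a visit that alone has an effect gains essentially nothing. The gain depends on effects at other visits.
- **That the all-three-visits result is the main argument.** Power for significance at all three visits is 59% with Bonferroni and 76% with Holm (38 per arm, 12/12/12, correlation 0.5). But a claim that requires every visit to be significant needs no adjustment: testing each at .05 gives about 77%. The article also does not say that all three must succeed jointly.
- **That a share of alpha is spent on baseline.** Baseline is a level of the time factor, but the article does not give the number of comparisons. A condensed article may leave that to a fuller document.
- **That Holm would repair the sizing.** The 29 per arm was derived for one comparison at .05, and Holm's first step remains at .0167.

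**Conclusion.** The point holds as a cheap improvement and not as an error. The named correction is valid, but Holm is never less powerful at the same familywise error and is more powerful under the pattern that the trial hypothesises. The gain is about 7 to 8 percentage points per visit when 12 points hold throughout, and about 13 points at 12 months under a 12/10/8 pattern. It falls to essentially zero when only one visit has an effect. These figures rest on a family of three post-baseline comparisons, the protocol's SD of 16 and an assumed between-visit correlation of 0.5.

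The smaller group size deserves attention. The Power Analysis section allows for dropouts before the 4-week follow-up, while the Discussion expects further loss over the year, so the later comparisons may be made with fewer than 38 per arm.

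**What to change.** Replace the post hoc sentence with wording such as: *The between-arm NDI differences at 4 weeks, 6 months and 12 months form one family of three comparisons; the baseline comparison is not part of it. They will be tested with Holm's step-down procedure at a familywise two-sided .05.*

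This costs one sentence, with no new data and no extra patients, and should be settled before unblinded data are seen. The downside is that Holm has no simple matching simultaneous confidence intervals. Report ordinary 95% intervals beside the Holm-adjusted p values, labelled as unadjusted, or add Bonferroni intervals as a supplement.

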### Power Analysis

Sample size and power calculations were performed using G*Power version 2 statistical software (Heinrich-Heine- Universität Düsseldorf) based on the minimal clinical improvement of 12 points on the NDI [51,69], assuming a standard deviation of 16 points, two-tailed, and an alpha level of .05. This requires a minimum sample size of 29 subjects per group. A total of 76 patients with a primary complaint of neck pain who meet the inclusion/exclusion criteria and consent to participate will be enrolled into the study. This sample size will yield greater than 80% power to detect both statistically significant and clinically meaningful changes in the NDI; additionally, this will control for dropouts prior to the 4-week follow-up.

### Risks

The risks associated with a patient’s participation in this study are minimal. Patients may experience an increase in pain intensity from completing the range of motion exercise due to a muscle or ligament injury. Based on our clinical experience, the chance of this happening is rare, which means it occurs in less than 1% of people. We have attempted to minimize this risk by having a licensed physical therapist examine all patients and instruct them in the proper exercise technique. In addition, a therapist will re-examine a patient at any time, if appropriate. It is also possible that patients will experience mild muscle soreness after the manipulation is performed. Based on our clinical experience, the chance of this happening is common, which means it occurs in 1%-25% of people. However, this soreness typically resolves within 1-48 hours after manipulation. We have minimized the risks associated with manipulation by ensuring that the licensed physical therapists participating in this study already routinely use manipulation in the management of patients with neck pain. We have further minimized this risk by ensuring that each physical therapist participating in this study has been specifically trained in the use of the manipulation techniques to be used in this study. Furthermore, all potential subjects will be screened to ensure they do not exhibit any exclusion criteria that may place the individual at increased risk for a serious complication.

When dry needling treatment is performed, it is possible that patients will experience the following common adverse events: bruising, bleeding, pain during treatment, pain after treatment, or aggravation of symptoms 1.7%-7.6% of the time (~2-8 out of 100). Uncommon adverse events include the following: drowsiness, headache, or nausea 0.13%-0.26% of the time (~1-3 out of 1000). Possible rare adverse events include fatigue, altered emotions, shaking, itching, claustrophobia, or numbness 0.01%-0.04% of the time (1-4 out of 10,000). Dry needling is very safe; however, the most serious side effect from dry needling is pneumothorax (ie, lung collapse due to air inside the chest wall), which can occur in less than 0.01% (<1 out of 10,000) treatments. This risk is very low and in a recent survey of physical therapists who use dry needling, Brady et al reported that no episodes of pneumothorax occurred in over 7600 treatments. We have minimized the risks associated with dry needling by ensuring that the licensed physical therapists participating in this study already routinely use dry needling in the management of patients with neck pain. We have further minimized this risk by ensuring that each physical therapist participating in this study has been specifically trained in the use of the dry needling techniques to be used in this study. Furthermore, all potential subjects will be screened to ensure they do not exhibit any exclusion criteria that may place the individual at increased risk for a serious complication.

Should any adverse event occur, it would be appropriately managed by the treating physical therapist by activating emergency services if immediate medical attention is required; standard clinical advice will be used in the case of minor events, such as transient soreness.

## Results

This trial is registered at ClinicalTrials.gov (NCT02731014) and recruitment is currently underway and is expected to be completed by the end of 2017. Data collection for long-term outcomes will occur throughout 2017 and 2018. Data analysis, preparation, and publication submission is expected to occur throughout the final three quarters of 2018. See Table 5 for the study timeline and milestones.

**Table 5 table5:** Timeline and milestones.

Activity	2016 (quarter)		2017 (quarter)				2018 (quarter)			
	3	4	1	2	3	4	1	2	3	4
Participant recruitment	X	X	X	X	X	X				
Data collection for long-term outcomes			X	X	X	X	X	X	X	X
Data analysis, preparation, and submission for publication								X	X	X
Publication submissions										X

## Discussion

### Principle Findings

Neck pain is commonly unresponsive or does not fully resolve with current treatment strategies, with 37% of patients going on to experience chronic neck pain of greater than one year [2]. Dry needling may be one intervention that could lead to improved outcomes when used in conjunction with exercise and manual therapy [11,39]. Anecdotally, in the clinical setting, a patient’s pain level commonly limits their ability to participate in active exercise interventions. As dry needling appears to have a significant treatment effect on reducing pain and increasing pressure pain threshold [38], it may facilitate a patient’s ability to perform a prescribed exercise program. In addition, it may improve patient compliance with exercise, which may lead to improved results from an exercise program.

Therefore, the aim of this trial is to determine if the addition of dry needling to an exercise and manual therapy treatment program will further reduce pain and improve disability in patients with mechanical neck pain, as compared to exercise and manual therapy and sham needling.

We hypothesize that patients who receive dry needling, manual therapy, and exercise will achieve greater reductions in pain and disability in the short term (ie, 4 weeks) and long term (ie, 6 and 12 months) compared to those who receive sham dry needling, manual therapy, and exercise.

As the use of dry needling by physical therapists becomes more widespread, and more therapists are trained in this approach, research is needed to support or refute its effectiveness. The results of this trial will assist in providing long-term outcomes examining the effectiveness of dry needling, which are currently lacking in the literature.

We anticipate the potential challenges to this study to include the following: difficulty with patient recruitment, patient compliance with follow-up schedule, and patients lost to follow-up over the 1-year, long-term, follow-up period. To address these challenges, we have utilized two large clinics in different locations in the United States to improve the ability to recruit patients in a timely manner. Further, we will provide a small financial reimbursement for patients as incentive for completion of the 4-week, 6-month, and 12-month follow-up in order to assist with compliance and reduce the numbers lost to follow-up.

### Limitations

We recognize that there are a number of potential limitations in the study design. The treating therapists cannot be blinded to group assignment, which may influence the verbal and nonverbal interaction with subjects. To try to manage this limitation, all therapists will be trained to maximize the consistency with which the dry needling intervention and the sham intervention will be performed.

We have chosen to allow therapists to perform individualized dry needling treatment specific to each patient within the outlined treatment algorithm to be consistent with clinical practice and improve external generalizability. We believe that providing treatment specific to the patient’s presentation will improve outcomes. We understand this may be seen as a limitation as it may lead to variation in the treatments that will be applied by therapists, which may mask the difference between groups. However, individualized treatment better reflects clinical practice.

Another potential limitation is that we are not including physical measures such as range of motion or pain pressure threshold in our analyses. We have chosen to limit our outcomes to validated questionnaires in an effort to decrease loss to follow-up, especially at the long-term time points.

## Appendix

Multimedia Appendix 1 APTA Grant review peer review report.

Multimedia Appendix 2 CONSORT‐EHEALTH checklist (V.1.6.1).

## Abbreviations

GROC: Global Rating of Change Scale
ICC: inter-class correlation
MTEX-Needle: manual therapy, exercise, and dry needling
MTEX-Sham: manual therapy, exercise, and sham dry needling
MTrP: myofascial trigger point
NDI: Neck Disability Index
VAS: Visual Analog Scale
